**ABBREVIATIONS/DEFINITIONS**

- NA

**STUDY SUMMARY**

| **Study Title** | The Effect of a Home-Based HIIT Intervention on Increasing Exercise among Low Active Adults |
| --- | --- |
| **Study Design** | The purpose of this study is to examine the effect of a home-based HIIT intervention on exercise among low active adults (defined as engaging in exercise 90 minutes or less per week). Participants will be randomly assigned to a HIIT-based intervention or a wait-list control each lasting 12 weeks (participants in the wait-list control condition will have the option of receiving the HIIT intervention following the 12 weeks). |
| **Primary Objective** | To examine the effect of a HIIT intervention on exercise minutes per week. |
| **Secondary Objective(s)** | To examine the effect of a HIIT intervention on weight and key psychosocial variables related to exercise. |
| **Research Intervention(s)/Investigational Agents** | HIIT is defined as an exercise protocol that intersperses a short period of high-intensity exercise with short periods of rest. The HIIT intervention will be designed to increase high intensity activity (70-85% of maximum heart rate) and will focus on engaging in exercises based on the participant’s current fitness and strength level. Even though high intensity is the goal, the participant will take frequent breaks throughout the exercise session to offset the high intensity nature of the exercises and potentially increase enjoyment of the exercise session. The participant will participate in eight telephone sessions over the 12 weeks that will instruct the participants on the home-based sessions and to motivate the participant to adhere to the exercise program. |
| **Scientific Assessment** | Not required, Minimial Risk Study |
| **IND/IDE # (if applicable)** | N/A |
| **IND/IDE Holder** | N/A |
| **Investigational Drug Services # (if applicable)** | N/A |
| **Study Population** | The target population will be individuals who exercise 90 minutes or less each week and do not have any health conditions that would limit exercise. |
| **Local Sample Size (number of participants recruited locally)** | 50 |

# Objectives

- 1. The purpose of this study is to examine the effect of a home-based HIIT intervention on exercise among low active adults (defined as engaging in physical activity 90 minutes or less per week). Participants will be randomly assigned to a HIIT-based intervention or a wait-list control each lasting 12 weeks (participants in the wait-list control condition will have the option of receiving the HIIT intervention following the 12 weeks).

# Background

- 1. Significance of Research Question/Purpose: A majority of previous studies have examined the effect of moderate-intensity exercise; however, few studies have examined the effect of home-based high intensity interval training on exercise adherence among low active individuals.
  2. Preliminary Data: N/A
  3. Existing Literature: High Intensity Interval Training (HIIT) consists of short repeated periods of intense effort (approximately 80-90% of an individual’s maximum heart rate) with recovery intervals in-between. HITT requires just a fraction of the time that is required for moderate intensity training (MIT; approximately 10-20% of the time commitment), and, therefore, addresses the “lack of time” barrier (Burgomaster et al., 2008; Gibala et al., 2006; Gibala, Little, Macdonald, & Hawley, 2012). Researchers have found that HITT leads to comparable or superior improvements in cardiometabolic health outcomes when compared to moderate intensity exercise. Results of studies have been mixed (Gibala et al., 2012), however, HIIT interventions have similar improvements in skeletal muscle metabolic adaptations, cardiovascular fitness, vascular function, glycemic control, and body composition when compared to a much higher volume of MIT (Gibala et al., 2012; Gist, Fedewa, Dishman, & Cureton, 2013; Hazell, Hamilton, Olver, & Lemon, 2014; Macpherson, Hazell, Olver, Paterson, & Lemon, 2011). Since much of the research is mixed and few studies have examined home-based HIIT exercise, this study will make a significant contribution to the literature.

# Study Endpoints/Events/Outcomes

- 1. Primary Endpoint/Event/Outcome: Exercise minutes per week as assessed by an accelerometer for one week at baseline, 6 weeks, and 12 weeks.
  2. Secondary Endpoint(s)/Event(s)/Outcome(s): Self-reported weight and height; psychosocial variables assessed via a questionnaire including social support for exercise, self-efficacy, enjoyment, and outcome expectancies.

# Study Intervention(s)/Investigational Agent(s)

- 1. Description: The intervention will be a 12-week high intensity interval training workout that will consist of home-based exercise sessions prescribed by the exercise counselor. The exercise sessions will be based on exercises the participant can confidentially engage in (regular push-ups vs. knee push-ups vs. wall push-ups). The goal will be to engage in three exercise sessions per week. The participants will receive weekly telephone calls during the first month and bi-weekly calls during months 2 and 3. The exercise counselor will also engage in dialogue that will motivate the participant to exercise. Specifically, the intervention will be based on Self-Determination theory, which is the idea that individuals are more likely to adhere to exercise if they are intrinsically motivated to increase their exercise. According to SDT, intrinsic motivation is enhanced by having a choice and opportunities for self-direction. Although we do not give participants a choice of exercises, we will give them a choice of when they exercise and in what order they complete the exercise sessions. The counseling sessions should be a collaboration between the counselor and participant on how to best integrate exercise into the participant’s daily routine. The counselor will also utilize strategies that will help the individual increase their enjoyment of physical activity.
  2. Drug/Device Handling: NA
  3. Biosafety: NA
  4. Stem Cells: NA

# Procedures Involved

- 1. Study Design: Low active adults will be randomly assigned to either a 12-week home-based high intensity interval training exercise intervention or a wait-list control condition to examine the effect of the intervention on exercise minutes per week.
  2. Study Procedures:

Step 1: Telephone Screening, Consent, and Baseline Questionnaires: In response to an advertisement, potential participants will call, email, or text a study line, at which time they will complete a telephone screening interview with the Research Assistant (RA) to determine eligibility for the study. Participants who are eligible will be given detailed information about the study and the consent form will be reviewed. The RA will schedule a randomization appointment in two weeks. Participants will be told that they may need to cancel the appointment if the online consent and questionnaires are not completed.

1. Complete telephone screening
   1. If not eligible, end interview and thank them for their time
   2. If eligible:
      1. Schedule randomization appointment for 2 weeks
      2. Email link to consent form and questionnaires
      3. Explain ActiGraph procedures. The actigraph is a small device that is attached to the participant’s clothing/belt at the waist and measures physical activity amount and intensity. The actigraph functions as a method of measuring physical activity with the purpose of obtaining objective measurement of the participants’ physical activity.

Step 2: Send ActiGraph: Upon completion of the online consent form and questionnaires, send the ActiGraph with instructions and return envelope.

Step 3: Check on consent and questionnaires

1. If the ActiGraph is not received by the randomization appointment, the participant is to be called to cancel the appointment. The participant should be told that they will be called to reschedule the appointment once the ActiGraph is received.
   1. Once the ActiGraph is received, call the participant to schedule a time or if time permits, complete the randomization appointment at the time of the initial call.
   2. If the ActiGraph has been received, proceed with the scheduled randomization appointment.

Step 4: Baseline Session

1. Participants are randomly assigned to either the exercise or wait-list control condition. The wait-list control condition will have the option of receiving the exercise intervention after the 12 weeks. The exercise intervention will be delivered via phone. Enter randomization date in REDcap.
2. Script: “The next thing we are going to do is to find out which of the two groups you have been randomly assigned to. This is completely random and unfortunately I have no control over which group you are assigned to. Let me access my form here to determine which program you are in.”
3. Exercise: “You have been randomly assigned to the exercise program. This program is designed to help you increase your exercise. I will work with you to make a plan on how you are going to fit exercise into your day. Do you have any questions before we start?”
4. Wait-List Control: “You have been randomly assigned to the wait-list control condition. This means that you will be contacted again in 12 weeks to complete your assessment. After your assessment, you will complete the exercise program if you would like to.”

Step 5: Intervention Sessions

- 1. The participant will be told when exercise should be stopped for safety reasons in order to minimize risk to the participant. See the intervention protocol (a supporting document) for more information. The intervention sessions will be audiotaped for quality control purposes.

**Step 6: 6 week assessment**

1) At 6 weeks, the participant will be prompted to complete the 6 week questionnaire.

Step 7: 12 week assessment

1. At 11 weeks, the participant will be mailed to the ActiGraph, which will be worn for one week starting the day after the last intervention session.
2. At 12 weeks, the participant will be prompted to complete the 12 week questionnaire.
3. The participant will be sent a $50 visa card once the 12 week assessment is complete and the ActiGraph is received.
   1. Study Duration: The study will last 12 weeks for the participant. We anticipate that it will take 12 weeks to enroll all participants and an additional 18 weeks to complete the sessions, 12-week follow-up, and data analysis.
   2. Individually Identifiable Health Information: N/A
   3. Use of radiation: N/A
   4. Use of Center for Magnetic Resonance Research*:* N/A

# Data and Specimen Banking

N/A

# Sharing of Results with Participants

- 1. Results will not be shared with participants.

# Study Population

- 1. Inclusion Criteria: 18 and older; exercising for 90 minutes or less each week; access to the Internet
  2. Exclusion Criteria: Specific exclusion criteria will include a history of coronary heart disease (history of myocardial infarction, symptoms of angina), orthopedic problems that would limit physical activity participation, diabetes, stroke, osteoarthritis, and any other medical condition that may make physical activity unsafe or unwise. Other exclusion criteria will include current or planned pregnancy, psychosis or current suicidal ideation, and psychiatric hospitalization within the last six months.
  3. Screening: Participants will respond to advertisements via text, email, or phone. Participants will complete a telephone screening interview over the telephone to determine eligibility.

# Vulnerable Populations

- 1. Vulnerable Populations:

Children

Pregnant women/Fetuses/Neonates

Prisoners

Adults lacking capacity to consent and/or adults with diminished capacity to consent, including, but not limited to, those with acute medical conditions, psychiatric disorders, neurologic disorders, developmental disorders, and behavioral disorders

Approached for participation in research during a stressful situation such as emergency room setting, childbirth (labor), etc.

Disadvantaged in the distribution of social goods and services such as income, housing, or healthcare

Serious health condition for which there are no satisfactory standard treatments

Fear of negative consequences for not participating in the research (e.g. institutionalization, deportation, disclosure of stigmatizing behavior)

Any other circumstance/dynamic that could increase vulnerability to coercion or exploitation that might influence consent to research or decision to continue in research

Undervalued or disenfranchised social group

Members of the military

Non-English speakers

Those unable to read (illiterate)

Employees of the researcher

Students of the researcher

None of the above

- 1. Additional Safeguards: N/A

Here

# Local Number of Participants

- 1. Local Number of Participants to be Consented: 50

# Local Recruitment Methods

- 1. Recruitment Process: Participants will be recruited via online email advertisements and Craig’s List at the beginning of the study. Interested participants will call, text, or email our study line/email address and participants will be called to complete a telephone screening interview.
  2. Identification of Potential Participants: Participants will self-identify in response to the study advertisements.
  3. Recruitment Materials: Online and email advertisements will be used for the study. The advertisement is included in this IRB submission.
  4. Payment: Participants will received a $50 visa gift card after the 12 week assessment is completed and the ActiGraph is returned.

# Withdrawal of Participants

- 1. Withdrawal Circumstances: Participants will be withdrawn if they demonstrate inappropriate behavior towards the exercise counselor.
  2. Withdrawal Procedures: If the participant states that they would like to withdraw, the research assistant will clarify if they wish to withdraw from both the counseling sessions and follow-up assessments or just the counseling sessions. If the participant wishes to withdraw from both, the participant will not be contacted again. If the participant wishes to withdraw from the counseling sessions only, the research assistant will ask the participant if it is fine for us to contact them for their 6- week and/or 12-week follow-up session. If they say yes, they will be contacted again for this appointment.
  3. Termination Procedures: N/A.

# Risks to Participants

- 1. Foreseeable Risks: There are two risks associated with this study. First, it is possible that a participant would experience a cardiac arrest or some other medical event as a result of exercise. This risk is considered minimal. To address this risk, participants will be given safety instructions that state when they should stop exercising and seek medical help. The second risk is the participant could sustain an injury while exercising. This risk is also considered minimal and participants will be given only exercises that are safe for them. Additionally, to minimize the risk of injury associated with exercise, participants will be screened for orthopedic problems and other medical issues that may make exercise unsafe or unwise. Participants will be advised to use/wear appropriate gear for their chosen form of exercise. If an injury or change in medical status occurs during the study, the intervention will be withdrawn until the participant obtains written clearance from their healthcare provider to continue to engage in exercise.
  2. Reproduction Risks: N/A.
  3. Risks to Others: N/A.

# Potential Benefits to Participants

- 1. Potential Benefits: Exercise is related to numerous health benefits including reduced risk of heart disease, stroke, some types of cancer, and obesity. If the participant adheres to the exercise protocol, they could experience any of these benefits.

# Statistical Considerations

- 1. Data Analysis Plan: Between groups ANOVA tests will be used to determine if there are significant differences between the two groups on exercise minutes per week, weight, and the psychosocial variables.
  2. Power Analysis: This is considered a pilot study and therefore, a power analysis has not been completed.
  3. Statistical Analysis: See 15.1 above.
  4. Data Integrity: When completing the online questionnaires, participants will be prompted if they miss an item. They will not be allowed to submit their questionnaire until they have completed all items. The research assistant will also look over the ActiGraph data to make sure it has been worn each day and exclude any days it appears it has not been worn.

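### Section 15.1 names a between-groups ANOVA on exercise minutes with no baseline adjustment, giving up precision that the baseline accelerometer week could supply

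*Protocol*

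**What the plan says.** Section 15.0 (Statistical Considerations), item 1, gives the whole analysis in one sentence: "Between groups ANOVA tests will be used to determine if there are significant differences between the two groups on exercise minutes per week", with weight and the psychosocial variables added to the same list. Item 3 of that section adds nothing further: "Statistical Analysis: See 15.1 above". No covariate, change score, group-by-time term or analysis time point is named.

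Section 3.0 (Study Endpoints) defines the primary endpoint as "Exercise minutes per week as assessed by an accelerometer for one week at baseline, 6 weeks, and 12 weeks". Under Procedures Involved, Step 3, the randomization appointment is cancelled if the ActiGraph has not come back, and otherwise: "If the ActiGraph has been received, proceed with the scheduled randomization appointment". Questionnaires are also completed before randomization, under the title "Step 1: Telephone Screening, Consent, and Baseline Questionnaires". The secondary endpoints are "Self-reported weight and height; psychosocial variables assessed via a questionnaire including social support for exercise, self-efficacy, enjoyment, and outcome expectancies".

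On size, Section 10.0 says "Local Number of Participants to be Consented: 50". The Baseline Session text describes random assignment with no allocation ratio and no stratification.

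**The concern.** The trial obtains a week of accelerometer data from participants before they are randomized, then names an analysis with no place for it. People differ in habitual activity, and the part of that variation which persists from baseline to follow-up stays in the error term of a plain ANOVA. A baseline covariate would remove it.

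Two things are at stake. The first is precision: the confidence interval for the group difference is wider than the collected data require. The second is chance imbalance. Nothing in the described randomization balances baseline activity, the arms are small, and an unadjusted comparison passes part of any baseline difference into the estimated effect.

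This is more than detail left for a SAP. The protocol makes a positive choice of test, and a SAP that followed it literally would run an unadjusted comparison.

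**Working it through.** The protocol states no effect size, SD or power, so there is no figure of its own to reproduce.

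**Inputs**
- Number consented: 50 (Section 10.0 and Study Summary).
- Allocation: not stated. Assumed 1:1, so n = 25 per arm at most.
- Significance level: not stated. Assumed two-sided 0.05.
- Effect: not stated. Assumed 0.6 SD of 12-week minutes, for illustration.
- Correlation r between baseline and 12-week minutes: not stated. Shown at 0, 0.3, 0.5 and 0.7.

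**Step 1. Unadjusted ANOVA at 12 weeks.** SE = SD × √(2/n) = SD × √(2/25) = 0.283 SD. For a 0.6 SD effect the noncentrality is 0.6/0.283 = 2.12. With 2n − 2 = 48 df, power is 55%. The effect detectable with 80% power is 0.81 SD.

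**Step 2. ANCOVA with baseline as covariate.** Its variance relative to Step 1 is (1 − r²) × [1 + 1/(2n − 4)], where the second factor is the small-sample cost of estimating the slope: 1 + 1/46 = 1.022. Error df are 2n − 3 = 47. The equivalent unadjusted total is 50 divided by the relative variance.

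| r | Relative variance | Equivalent unadjusted total | Power at 0.6 SD | Detectable at 80% power |
| --- | --- | --- | --- | --- |
| 0 | 1.00 × 1.022 = 1.02 | 49 | 54% | 0.82 SD |
| 0.3 | 0.91 × 1.022 = 0.93 | 54 | 58% | 0.78 SD |
| 0.5 | 0.75 × 1.022 = 0.77 | 65 | 66% | 0.71 SD |
| 0.7 | 0.51 × 1.022 = 0.52 | 96 | 82% | 0.58 SD |

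**Step 3. Chance imbalance.** The baseline mean difference, in baseline SD units, is approximately N(0, 2/n), with standard error 0.283.
- P(difference beyond 0.3 SD in either direction) = 2 × [1 − Φ(0.3/0.283)] = 29%.
- P(beyond 0.5 SD) = 2 × [1 − Φ(0.5/0.283)] = 8%.

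Given an observed imbalance, the unadjusted estimate shifts by r times its size. For 0.3 SD that is 0.3 × 0.3 = 0.09 SD up to 0.7 × 0.3 = 0.21 SD.

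**Step 4. If the ANOVA were run on change scores.** Relative variance is 2(1 − r): 1.40, 1.00 and 0.60 at r = 0.3, 0.5 and 0.7. ANCOVA has 0.93, 0.77 and 0.52. The change score is less precise than ANCOVA throughout this range, and less precise than plain ANOVA when r is below 0.5.

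**Step 5. Sensitivity to loss.** With an assumed 20% loss (20 per arm), the standard error of the baseline difference is √(2/20) = 0.316 SD, and the chance of exceeding 0.3 SD rises to 34%. Power at 0.6 SD falls to 46% unadjusted, against 48% at r = 0.3 and 56% at r = 0.5 adjusted.

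**The case against.** The strongest reply is that the planned test is not wrong. Under randomization, unadjusted ANOVA is unbiased on average and, over all randomizations, keeps its 5% type I error. This stands, and the point concerns efficiency only. A reader might infer that the plan inflates false positives, because the type I error given a 0.5 SD baseline imbalance is about 11% at r = 0.5 and 16% at r = 0.7. Those figures describe only the trials that happen to draw such an imbalance. Differences beyond 0.5 SD occur in about 1 trial in 13, so calling an imbalance of that size ordinary would overstate it.

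Second, the gain rests on an unknown r. The entry limit of 90 minutes or less per week may narrow the baseline spread and lower r, and at r = 0.3 the benefit is small. This also stands. But the worst case is a loss of about 2%, so the balance still favours adjustment.

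Third, the sentence is short and does not strictly exclude a change score. However, the variable it names is minutes, not change, and Step 4 of the working shows that a change score would be the weaker use of the baseline.

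Fourth, a reader might extend the point to say that every outcome has a recorded baseline and that weight is close to untestable as planned. The documents do not support this. A baseline is explicit only for accelerometer minutes. That the baseline questionnaires record weight and each psychosocial scale is a reasonable inference, but it is not stated item by item, and the protocol gives no SD, effect or correlation for weight. Randomization also depends on receipt of the device rather than on valid wear, so a usable baseline is likely for nearly everyone but not assured.

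Finally, this is a pilot without a power analysis, which lowers the weight of power figures. It does not remove the point, because the same section plans significance tests between the groups.

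**Conclusion.** The point holds as a matter of efficiency. Section 15.1 names an unadjusted between-groups test for a primary outcome whose baseline value the trial collects before randomization. The size of the loss is uncertain: modest if r is about 0.3, and substantial at 0.5 to 0.7, where adjustment would be worth about 15 to 46 extra participants in an unadjusted trial (65 − 50 and 96 − 50). Chance imbalance is a secondary argument.

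These figures assume 1:1 allocation, two-sided 0.05 and all 50 consented participants analysed. The 50 are counted at consent, before randomization, so the arms may be smaller, which makes chance imbalance more likely.

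**What to change.** In Section 15.1, state that exercise minutes per week at 12 weeks will be compared between the randomized groups by ANCOVA with baseline accelerometer minutes as covariate, and that the adjusted mean difference and its 95% CI will be reported. This also settles the time point of the primary comparison, which the sentence leaves open.

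Analyse weight and each psychosocial score in the same way, each with its own baseline value, where the baseline questionnaire records it. Confirm which items it contains before writing this in.

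The cost is a reworded sentence and one degree of freedom. No new data are needed.

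### The named between-groups ANOVA, run at 12 weeks, uses neither baseline nor 6-week values and can favour HIIT if HIIT dropout depends on earlier response

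*Protocol*

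**What the plan says.** Section 15.1 applies one method to all outcomes (accelerometer minutes, weight and the questionnaire scales): "Between groups ANOVA tests will be used to determine if there are significant differences between the two groups". It names no visit, baseline term or repeated-measures term. Section 15.3 (Statistical Analysis) adds only "See 15.1 above".

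The outcomes are scheduled more than once:

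- Section 3.1 places the accelerometer at baseline, 6 weeks and 12 weeks. Section 5, Step 6 mentions only a questionnaire at 6 weeks.
- Section 3.2 lists the secondary outcomes without visits: "Self-reported weight and height; psychosocial variables assessed via a questionnaire including social support for exercise, self-efficacy, enjoyment, and outcome expectancies".
- Section 5, Step 6: "At 6 weeks, the participant will be prompted to complete the 6 week questionnaire". Its contents are not given. Step 7: "At 12 weeks, the participant will be prompted to complete the 12 week questionnaire".

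Section 12.2 deals with withdrawal in two ways. For those leaving both counseling and follow-up: "If the participant wishes to withdraw from both, the participant will not be contacted again". Those leaving counseling only are asked whether they may still be contacted for the later assessments.

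Section 15.4 makes participants complete every item before submitting. That prevents missing items, not missing questionnaires.

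**The concern.** The design is longitudinal and the named test is cross-sectional. A between-groups ANOVA at week 12 compares only the people who have a week-12 value. If someone in the HIIT arm scores poorly at week 6 and then leaves, the week-6 score is informative about the missing week-12 score, but the test does not use it.

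Unequal loss is plausible from the design. During the 12 weeks only the HIIT arm has counseling to leave and a study exercise program that can cause injury. Controls are offered the program after their 12-week assessment, which is a reason to stay. Enjoyment and self-efficacy are themselves outcomes and could be reasons for leaving. If loss follows that pattern, the ANOVA compares the better-responding part of the HIIT arm with nearly all controls, and the error runs in favour of HIIT.

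**Working it through.** The protocol gives no SD, effect size, alpha or dropout rate, so there is no figure to reproduce.

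**Inputs.** From the protocol: 50 participants (section 10.1). Everything else is assumed: 25 per arm, outcome SD 1, and the correlations, loss rates and selection strengths below. The standard error of a 12-week difference with no loss is sqrt(2/25) = 0.28 SD.

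**Set A.** 4,000 trials per setting; true effect 0.25 SD at week 6 and 0.50 SD at week 12; the same correlation ρ between all visits; no control loss; HIIT loss after week 6 either random (0) or more likely with a worse week-6 value (log-odds 1 or 2 per SD). Bias in SD, for ρ = 0.5 / 0.7 / 0.9:

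| HIIT loss | Log-odds | ANOVA | Completers, baseline-adjusted | Likelihood using week 6 |
|---|---|---|---|---|
| 10% | 0 | -0.001 / -0.006 / 0.005 | 0.003 / -0.002 / 0.001 | -0.002 / -0.007 / 0.004 |
| 10% | 1 | 0.046 / 0.061 / 0.079 | 0.023 / 0.021 / 0.008 | 0.000 / -0.002 / -0.002 |
| 10% | 2 | 0.073 / 0.098 / 0.133 | 0.039 / 0.034 / 0.019 | 0.003 / -0.002 / 0.000 |
| 20% | 0 | 0.000 / -0.002 / 0.004 | 0.001 / -0.002 / -0.001 | 0.000 / -0.002 / 0.001 |
| 20% | 1 | 0.089 / 0.119 / 0.161 | 0.047 / 0.035 / 0.018 | 0.002 / 0.000 / 0.004 |
| 20% | 2 | 0.129 / 0.184 / 0.228 | 0.067 / 0.058 / 0.022 | -0.002 / -0.003 / -0.005 |
| 30% | 0 | 0.001 / 0.002 / -0.005 | 0.002 / 0.005 / -0.001 | 0.003 / 0.003 / -0.001 |
| 30% | 1 | 0.124 / 0.177 / 0.225 | 0.063 / 0.054 / 0.021 | -0.004 / 0.004 / -0.002 |
| 30% | 2 | 0.191 / 0.264 / 0.341 | 0.099 / 0.083 / 0.038 | 0.001 / 0.003 / 0.004 |

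**Set B.** 5,000-6,000 trials per setting; no true effect; correlations 0.6 (baseline to week 6), 0.5 (baseline to week 12) and 0.7 (week 6 to week 12); 10% random control loss; HIIT loss 24-35%, more likely with low week-6 scores. Three settings:

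- ANOVA: bias 0.146, 0.211, 0.267; type I error 7.7%, 9.9%, 11.9%.
- Completers, baseline-adjusted: bias 0.085, 0.126, 0.159; type I error 6.6%, 6.5%, 7.6%.
- Longitudinal likelihood: bias 0.001, 0.003, 0.004.

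A repeat with the same correlations and loss range (6,000 trials) gave +0.12 to +0.24 for ANOVA (type I error 6.6-11.5%), +0.07 to +0.14 after baseline adjustment, and within 0.01 for the likelihood model. The last result also held with no week-6 data in controls, which matters because the wait-list script in Step 4 mentions contact only at 12 weeks.

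**Why the sizes come out this way.** Let m be the mean week-6 value of HIIT stayers minus that of the whole arm, in SD.

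- ANOVA bias = ρ(6,12) × m. In set A at 30% loss and log-odds 2, 0.191/0.5, 0.264/0.7 and 0.341/0.9 all give m of about 0.38.
- Bias after baseline adjustment is about [ρ(6,12) - ρ(0,6) × ρ(0,12)] × m. Set A, ρ = 0.5: (0.5 - 0.25) × 0.38 = 0.095 (simulated 0.099). Set A, ρ = 0.9: (0.9 - 0.81) × 0.38 = 0.034 (simulated 0.038).
- Set B, worst setting: m = 0.267/0.7 = 0.38, and (0.7 - 0.6 × 0.5) × 0.38 = 0.152 (simulated 0.159).

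Baseline adjustment thus removes about 40% of the bias in set B (1 - 0.159/0.267 = 0.40), and about 48% to 89% in set A at 30% loss and log-odds 2 (1 - 0.099/0.191; 1 - 0.038/0.341).

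**Precision under random loss.** In set B the SD of the estimate falls from 0.315 (ANOVA) to 0.265 (longitudinal). Baseline adjustment alone would give 0.315 × sqrt(1 - 0.5²) = 0.273, so most of the gain comes from baseline.

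**The case against.** The strongest reply is that the bias is built into the assumptions. The simulated HIIT arm loses its worse week-6 responders, and the data are missing at random given week 6, so the longitudinal model is bound to do well. The protocol states no dropout rate, no difference between arms and no mechanism. That is correct, and it makes the point conditional.

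Several stronger readings might be inferred, and the text does not support them:

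- *The plan discards the 6-week data.* Section 15.1 names no visit, so a separate 6-week ANOVA would fit. What is absent is joint use of the visits.
- *The plan imposes a completer analysis.* No such rule is stated. ANOVA can follow imputation, and the handling of missing visits may sit in an SAP that was not available.
- *Dropout is expected.* Section 12.2 only provides for it. It seeks follow-up from people who stop counseling only, and the $50 payment is tied to the 12-week assessment and return of the ActiGraph. Both work against loss.
- *Weight and the psychosocial scales are measured at week 6.* The contents of that questionnaire are not given. If they are absent, there is no week-6 value to use for them.

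It is also fair to say that baseline adjustment does a good share of the work, that nothing here was computed for weight specifically, and that this is a pilot. Pilot status does not settle the matter, because section 15.1 still plans significance tests. The choice of test is stated in the protocol, so it can be judged without the SAP.

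**Conclusion.** The point holds in conditional form. The named method fits a repeated-measures design poorly, and a better one is available at little cost. Bias is possible, not certain:

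- random loss: about zero;
- HIIT loss of 10-35% that depends on the week-6 value: about +0.05 to +0.34 SD for ANOVA, or roughly 0.16 to 1.2 standard errors (0.046/0.283; 0.341/0.283);
- the same mechanism after baseline adjustment alone: about +0.07 to +0.16 SD at 24-35% loss in set B and its repeat, and +0.02 to +0.10 SD at 30% loss with equal correlations;
- longitudinal likelihood model: within about 0.01 SD, under missing at random.

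All inputs except the 50 participants are assumptions. For an outcome very highly correlated between visits, baseline adjustment removes most of the bias and week 6 adds little.

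**What to change.** In section 15.1, replace the ANOVA with one linear mixed model per outcome:

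- Use the baseline value and every follow-up value actually collected for that outcome. For accelerometer minutes these are the visits in section 3.1, once reconciled with Step 6. For weight and the psychosocial scales, include week 6 if the 6-week questionnaire contains them, and state whether it does.
- Fit group-by-time with a common baseline mean and unstructured covariance.
- Include every randomized participant with any value, and report the 12-week group difference.

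The cost is two sentences in section 15.1 and a standard routine, with no new data. With three visits the covariance has six parameters (three variances, three covariances). The model relies on missing at random, which is weaker than what a completer ANOVA needs, but it does not correct dropout driven by unseen 12-week values. If an outcome has no 6-week value, the model becomes essentially a baseline-adjusted comparison and the benefit from week 6 is lost for that outcome.
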